### Image acquisition protocol & innovative photo robot

The trial protocol includes image acquisition protocol to minimize variability of patient’s imaging. The clinical partners will have an option to use a “Photo Robot” which is a special photo booth that includes a standardized setting for image acquisition and uploads an anonymized image to the CINDERELLA-platform. The Photo Robot is a prototype manufactured especially for the trial by a team with extensive experience in multiple photographs of complex and small sized objects and the reconstruction of 3D imagery.

### Statistical analysis

Once the data set is collected, an initial treatment ("cleaning") will be performed to eliminate potential inconsistencies, e.g. poorly completed questionnaire items, a broad characterization taking into account the dropout of patients or censored observations, and a comprehensive descriptive analysis of the data, namely looking for patterns in the data and corresponding hypotheses of interest for the inferential analysis.

For the primary objectives of the trial, models of the class of generalized linear models (in particular, multinomial regression models for ordinal data) will be fitted in order to evaluate the effect of the training and the women’s characteristics on their evaluation of the aesthetic outcome of the surgery. In order to assess the improvement in the ability to classify the aesthetic result of their surgery provided by training, Weighted Cohen’s k will be calculated for both groups (train and control) and compared using a statistical test and/or bootstrap techniques. A measure of similarity between self-evaluation and the BCCT.core will be computed for each participant and a beta regression model will be fitted to assess the effect of training, controlled by variables that can play as confounders such as women’s and disease’s characteristics at each time point and in a longitudinal perspective.

Analysis of the secondary objectives: (i) Patient’s body image satisfaction after surgery; (ii) Resource consumption (time spent in hospital, number of appointments, duration until treatment, additional care sought by patients) and CO_2_ emissions in both the intervention and the control arm; (iii) Patient’s satisfaction with their professional life; (iv) Patient’s sexual life satisfaction; (v) Patient’s general health-related quality of life, the patient-reported outcome measures administered will be scored according to the official guidelines provided by the developers of the instruments. Utility values will be derived from the preference-based EQ-5D-5L questionnaire, based on the value set recently derived from a representative sample of the Italian population [15]. In this context, the collected data will also be analysed in an exploratory way after a potential cleaning and an elimination of inconsistencies. Unitary costs will be expressed as EUR 2023. Unitary costs will be derived from national price listings or in patient official tariffs, laboratory and instrumental tests will be valued according to the outpatient procedures formulary in accordance with the ongoing policies at the five centers. Taking account of the type of outcomes under study, adequate statistical analyses will be carried out again using generalized linear mixed models that are implemented in several R-specific packages ® [R Core Team, 2022]. All the statistical analysis will be conducted using R statistical software. The longitudinal character of some outcomes will allow estimating their profiles by detecting trends. All processes and analyses will be clearly documented for reproducibility purposes.

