Newly diagnosed breast cancer patients are put in the position of having to make difficult decisions several times during their treatment journey [2]. Current treatment approaches are multimodal, including surgery, systemic therapy, and radiation [3]. Patients might be given a choice for sequencing therapy (e.g., systemic therapy before or after surgery) that may influence the type of locoregional therapy (e.g., from mastectomy to breast conservation). In each modality, the patients might be offered different choices of therapy (e.g., different systemic agents, mastectomy or oncoplastic surgery), based on their personal risk factors (e.g., age, comorbidities) and disease-related factors (e.g., stage, molecular subtype) and physician preference. Surgical management is no longer the one-size-fits-all mutilating procedure of radical (even if modified) mastectomy that governed breast surgery for almost 100 years, but evolved to offer better aesthetic outcomes, improved quality of life (QoL) and psychological well-being of patients [4, 5]. For a given breast cancer stage, the patient might be offered different types of breast and lymphatic surgeries and various radiation protocols, with similar oncological outcomes, which might be challenging to explain to the patient [2, 5]. Based on the patient’s individual risks/factors (e.g., smoking, body mass index), location of the primary tumour, surgical procedure and surgeon’s expertise, and whether radiation was applied, the aesthetic outcomes might vary significantly between patients undergoing the same treatment [6].

Current practice for deciding on locoregional therapy and shared decisions varies between centres and may include pictures, drawings, brochures, referral to the centre’s website, and a meeting with a variety of staff members, but it is not uniform and does not consider all the patient’s individual factors. In addition, breast cancer patients who refer to social media or unsupervised websites for information may be subjected to misinformation [7]. Social media can be particularly persuasive as it is used daily to access a wide range of information including medical information. Moreover, the information has an emphasis on visual content and personal experiences [7]. Thus, this misinformation might challenge the shared decision process of the patient and her caregiver.

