## Methods

Prospective randomized international multicentre parallel group trial conducted in 5 clinical centres, each attaining an institutional ethics approval. All patients will need to sign a written informed consent form. Randomization will be performed centrally, 1:1 to control arm (conventional current clinical practice for patient education prior to therapy) or intervention arm. Randomization will follow the minimization method proposed by Pocock and Simon [11, 12], a covariate-adaptive randomization procedure that achieves balance within covariate margins. The randomization procedure requires randomization lists of two types: (1) 50:50 lists, with blocks of size two will be used to assign the patients when balance between groups is attained during the randomization process. (2) Unbalanced 20:80 and 80:20 randomization lists in blocks of size five will be used to assign the patients otherwise (Fig 1).

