**Primary objectives:** 1. To evaluate the difference between both arms of the trial, regarding the match of expectations about the aesthetic outcome before and after treatment. 2. Experimental arm only, the agreement of the pre-treatment AI-evaluation (output) and patient’s post-therapy self-evaluation. **Secondary objectives:** 1. To evaluate the difference, between both arms of the trial, in patient’s body image satisfaction after surgery. 2. To evaluate the difference between both arms of the trial, in health resource consumption (time spent in hospital, number of appointments, duration until treatment additional care sought by patients). 3. To evaluate the difference, between both arms of the trial, in patient’s satisfaction with their professional life. 4. To evaluate the difference between both arms of the trial, in patient’s satisfaction with their sexual life. 5. To evaluate the difference, between both arms of the trial, in patient’s satisfaction with their general health-related quality of life.

Stratification will be considered to balance potential confounding factors that might influence aesthetic outcomes, i.e., type of surgery (conservative, mastectomy), patient age (<50, 50+) and radiotherapy (yes, no) (see flowchart in Fig 1). This randomization procedure was implemented and simulated using R, a free software environment for statistical computing and graphics (R Core Team, 2022 ®), following the minimization method proposed by Pocock and Simon [11, 12], a covariate-adaptive randomization procedure that achieves balance within covariate margins. The randomization was designed to be implemented in each of the centres and then, integrate the trial as a whole.

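### Allocation is implemented by centre and the comparator varies by centre, but the primary analyses name no centre term and define one pooled weighted kappa per arm

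*Protocol article*

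**What the plan says.** **Design.** The first sentence of Methods describes a "Prospective randomized international multicentre parallel group trial conducted in 5 clinical centres". The same paragraph has randomization done centrally, and the paragraph after Table 1 adds: "The randomization was designed to be implemented in each of the centres and then, integrate the trial as a whole". The listed balancing factors are type of surgery, age group and radiotherapy. Centre is not among them.

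**Comparator.** The control arm receives "conventional current clinical practice for patient education prior to therapy". The Introduction says of such practice: "Current practice for deciding on locoregional therapy and shared decisions varies between centres".

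**Primary analyses (Statistical analysis, second paragraph).**
- The ordinal regression is fitted "in order to evaluate the effect of the training and the women’s characteristics on their evaluation of the aesthetic outcome of the surgery".
- Weighted kappa is computed once in each arm, and the two values are compared by a test, a bootstrap or both.
- The beta regression for similarity between self-evaluation and BCCT.core is "controlled by variables that can play as confounders such as women’s and disease’s characteristics".

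Centre is named in none of the three. Generalized linear mixed models appear in the next paragraph, on the secondary objectives, without a stated grouping factor.

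**The concern.** When allocation is organised within centres, each centre contributes its own comparison of the arms, and differences between centres drop out of the estimated arm effect. An analysis that ignores centre leaves those differences in the error term. Its standard error is then larger than the true sampling variation, so intervals are too wide and the test is conservative.

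For kappa, the quantity itself can change. Kappa compares observed disagreement with the disagreement expected from the margins. If women in some centres both expect more and rate the result higher, pooling the centres widens the margins, raises the expected disagreement and so raises kappa. The pooled figure then contains agreement between centres as well as agreement between women treated in the same centre.

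The comparator adds a practical reason to look by centre: if control practice varies, a single pooled contrast does not show where the platform adds something.

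**Working it through.** **1. The plan's own figure.** Sample size per arm is 515 after a 40% dropout correction (Methods, paragraph before Table 1).
- 309 / (1 − 0.40) = 515 exactly. The alternative, n × 1.40, misses it: 367 × 1.40 = 513.8 and 368 × 1.40 = 515.2.
- So 309 evaluable women per arm is the consistent reading. The 309 cannot itself be reproduced, because the expected kappa, the category shares and the weights are not given. Under assumed values, a half-width of 0.1 needs about 70 to 390 per arm.
- Centre plays no visible part in this figure, and the point does not change it.

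**2. Precision of the arm comparison.** Inputs: 309 per arm, arms balanced within centre, two-sided 5%, effect set to give 80% power with a centre term. The centre ICC is assumed, since the article gives none. On a linear approximation:
- CI width ratio (without / with centre): r = 1 / √(1 − ICC).
- Power without centre: Φ(1.960 + 0.842 − 1.960 r).
- Type I error without centre: 2 × [1 − Φ(1.960 r)].

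| Centre ICC | CI width ratio | Power | Type I error |
|---|---|---|---|
| 0.02 | 1.010 | 79.4% | 4.8% |
| 0.05 | 1.026 | 78.5% | 4.4% |
| 0.10 | 1.054 | 76.9% | 3.9% |
| 0.20 | 1.118 | 72.9% | 2.8% |

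**3. Pooled against within-centre kappa, linear weights.** Assumptions: five equal centres, four grades with shares 10/23/42/25%, latent correlation 0.4, unit residual variance. Centre shifts are normal with SD s, so ICC = s² / (1 + s²).

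| Centre SD s | ICC | Shifts in the two ratings | Pooled | Within centre | Difference |
|---|---|---|---|---|---|
| 0.165 | 0.03 | shared | 0.244 | 0.235 | +0.009 |
| 0.33 | 0.10 | shared | 0.267 | 0.234 | +0.033 |
| 0.5 | 0.20 | shared | 0.296 | 0.233 | +0.063 |
| 0.5 | 0.20 | unrelated | 0.186 | 0.185 | +0.001 |

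Quadratic weights are more sensitive. With latent correlations of 0.3 and 0.5, shared shifts give about +0.01 at ICC 0.02, +0.03 at 0.05, +0.05 to +0.07 at 0.10 and +0.10 to +0.13 at 0.20. If centre shifts one rating only, the difference is between −0.002 and 0 throughout. For scale, the article plans kappa with a precision of 0.1.

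**4. Between-arm difference in kappa.** Quadratic weights, latent correlation 0.3 in one arm and 0.5 in the other, same shared centre shifts in both arms.

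| Centre ICC | Pooled | Within centre | Pooled minus within |
|---|---|---|---|
| 0.02 | 0.174 | 0.177 | −0.003 |
| 0.05 | 0.170 | 0.178 | −0.008 |
| 0.10 | 0.159 | 0.174 | −0.015 |
| 0.20 | 0.143 | 0.175 | −0.032 |

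At ICC 0.10 the single-arm kappas rise by 0.065 and 0.051 through pooling, while their difference moves by only 0.015. Most of the inflation cancels, and what remains shrinks the contrast.

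**The case against.** **The article does not exclude centre.** The ordinal-model sentence states a purpose, not a formula. The beta regression list is open (it gives examples), and the mixed models are introduced with the word again. A full covariate list may stand in an SAP that is not shown. This is right as far as it goes: the article names no centre term, and a reader who infers that one has been ruled out goes beyond the text. What remains is that the section does write out the effects of interest and fixes one kappa per arm, so an analysis that followed it would omit centre.

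**Allocation may not be by centre.** Methods also says "Randomization will be performed centrally, 1:1 to control arm", and centre is not a listed factor. The two statements are compatible, since a central service can run a procedure for each centre. If allocation were not balanced within centre, the gain from a centre term would remain: power without it would be 79.2%, 78.0%, 75.7% and 70.7% at the four ICC values.

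**Pooled kappa is legitimate.** A woman who expects good and receives good is a match whatever her centre; stratifying changes only the chance reference. This stands. The within-centre kappa is a different quantity, not a correction, so it belongs beside the pooled kappa and not in its place.

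**Two stronger readings are tempting.**
- A reader might infer that surgical skill is said to differ by centre. The Introduction names the surgeon's expertise as a source of variation between patients and does not mention centres there. The point does not need it.
- A reader might also expect centres whose expectations and results are out of step to pull pooled kappa below the within-centre value. They lower both alike (0.186 and 0.185), so stratifying recovers nothing in that case.

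**Conclusion.** The point holds in limited form. Allocation is described as implemented by centre and the comparator as varying by centre, yet no primary analysis names centre.

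For the arm comparison the cost is modest and in the safe direction. Intervals are 1% to 5% wider, with a loss of about three power points or fewer, for a centre ICC up to 0.10; at 0.20 they are 12% wider with a loss of about seven points. There is no excess of false positives.

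For kappa, the issue arises only if centre moves both ratings the same way. It then matters most for the second primary objective, agreement between the AI evaluation and self-evaluation in the experimental arm, where there is no second arm against which the inflation could cancel.

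Every size given here rests on an assumed centre ICC or SD and on equal centres. At the low end of the range the effects are negligible. The Introduction's remark on varying practice is general and does not describe the five sites one by one, so it supports looking by centre but does not establish how different the sites are. Low to moderate priority.

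**What to change.** In Statistical analysis, second paragraph:

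1. Add centre (five levels) as a term in the ordinal model and in the beta regression. The ordinal odds ratio for arm is then a within-centre one, and should be described so.
2. Resample within centre and arm in the bootstrap.
3. Beside the pooled weighted kappa, report a centre-stratified one: 1 − Σ w_c O_c / Σ w_c E_c. Here O_c and E_c are the observed and expected weighted disagreement in centre c, and the weights w_c are the same in both arms. Do this for both primary objectives.
4. Show the arm difference by centre descriptively.

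The cost is 5 − 1 = 4 degrees of freedom and some code. No new data are needed, and the sample size stays as it is.

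### The analyses stated for the primary objectives do not match those objectives: objective 2 has none, and objective 1 has one only if an unnamed kappa pair is read in

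*Protocol article*

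**What the plan says.** **Objectives.** Table 1 gives the first primary objective as "To evaluate the difference between both arms of the trial, regarding the match of expectations about the aesthetic outcome before and after treatment". The second is "Experimental arm only, the agreement of the pre-treatment AI-evaluation (output) and patient’s post-therapy self-evaluation". The Abstract and the sample size paragraph in Methods state the same two objectives in similar terms.

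**Analyses.** The Statistical analysis section has a paragraph expressly for the primary objectives. It plans three things:

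- A regression model for ordinal data, to "evaluate the effect of the training and the women’s characteristics on their evaluation of the aesthetic outcome of the surgery".
- An agreement comparison: "Weighted Cohen’s k will be calculated for both groups (train and control) and compared using a statistical test and/or bootstrap techniques". Its purpose is given as "In order to assess the improvement in the ability to classify the aesthetic result of their surgery provided by training".
- A beta regression, for which "A measure of similarity between self-evaluation and the BCCT.core will be computed for each participant".

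**Sample size.** The sample size paragraph names both primary objectives and says that the simulations used weighted kappa.

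**The concern.** A primary analysis should estimate the quantity that the primary objective names. Here the objectives concern expectation against outcome and AI grade against self-evaluation. The analysis paragraph concerns how a woman rates her result, how well she can classify it, and how close her rating is to a software score. These are different quantities. A platform could bring expectations closer to outcomes without changing how women rate themselves against BCCT.core, and the reverse is also possible.

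Two things are at stake. If the paragraph is followed literally, the trial would report no estimate for objective 2 and possibly none for objective 1. If the analysts depart from it, the final analysis will differ from the published protocol and may look chosen after the data were seen.

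**Working it through.** No figure in the article is in dispute, so the check sets the passages side by side.

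| Quantity | Where it is an objective | Where it is analysed |
|---|---|---|
| Expectation versus outcome, difference between arms | Primary objective 1 (Abstract, sample size paragraph, Table 1) | Not named. Possible only if it is the pair behind the kappa comparison |
| Pre-treatment AI grade versus post-therapy self-evaluation, experimental arm | Primary objective 2 (same places) | Not named. No single-arm agreement estimate is stated |
| Woman's evaluation of the outcome | Not a primary objective in its own right | Ordinal model |
| Ability to classify the result | None | Stated purpose of the kappa comparison |
| Self-evaluation versus BCCT.core | None, primary or secondary | Beta regression |

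**Step 1: can the ordinal model serve objective 1?** As described, its response is the woman's evaluation of the result. A match needs two ratings from the same woman. A shift in the evaluation alone does not show whether it came closer to what she expected.

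**Step 2: can the kappa comparison serve objective 1?** It can in form, because it is an agreement measure compared between two groups. But the two ratings are not given, and the stated purpose is classification ability, not the match of expectations. Table 2 collects expectations at all four time points, so expectation data will exist. The text does not connect them to the kappa.

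**Step 3: can BCCT.core stand for the AI grade of objective 2?** No, for two reasons.

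- *Timing.* Table 2 schedules BCCT.core at 6 and 12 months after the end of treatment, whereas objective 2 needs a pre-treatment grade.
- *Population.* The similarity measure is computed for every participant, whereas the AI grade arises only in the investigational arm, from a match to a repository case that BCCT.core has already classified.

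**Step 4: what is training?** The randomised contrast is platform against conventional patient education. The only other use of the word in the article concerns nurses at the sites. With two arms, one of them called control, the trained group must be the platform arm, but the article does not say so.

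**Step 5: is the AI grade available?** Table 2 has no row for it. The Methods say that the picture and its evaluation are supplied when the patient asks, and that matching fails when image quality is too low. Some experimental-arm patients may therefore have no AI grade.

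**The case against.** The strongest reply concerns objective 1. The sample size paragraph links weighted kappa to both primary objectives. The analysis section then compares weighted kappa between two groups in the paragraph for those objectives. Read together, the kappa comparison may well be the intended test of objective 1, with its pair of ratings left out. This stands as a possible reading, and it limits the point.

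It also rules out stronger conclusions that a reader might draw:

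- *That neither objective is analysed at all, or that the whole paragraph tests self-rating against BCCT.core.* BCCT.core is named only for the beta regression. The kappa pair is unnamed, not misnamed.
- *That the planned tests would have almost no power for objective 1.* That would assume the kappa pairs self-evaluation with BCCT.core and that the platform leaves this agreement unchanged. The article gives no kappa values, category shares or weights from which to work out such a loss.
- *That the training wording changes who is compared.* It does not. It is an undefined label for the platform arm.

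A further reply is that a condensed article leaves detail to the SAP. That is fair for weights, model form and bootstrap scheme. It does not cover this point, because the article does state analyses for its primary objectives and they are aimed elsewhere. For objective 2 there is no rescuing reading.

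**Conclusion.** The mismatch is real and should be corrected before analysis. Of the two primary objectives, objective 2 has no stated analysis. Objective 1 has one only on a reading that the paragraph does not give. One of the three stated analyses addresses a comparison that is no listed objective.

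The conclusion rests on the article's wording alone and on no assumed figures. An SAP that is not shown may already name the right ratings. If so, the published paragraph still has to be brought into line with it. No size in terms of power or bias can be given from the document.

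**What to change.** Rewrite the paragraph on the primary objectives in the Statistical analysis section, and keep the SAP consistent with it.

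- **Objective 1:** state that the between-arm comparison of weighted kappa uses the pre-treatment expectation rating and the post-treatment outcome rating, and name one time point.
- **Objective 2:** state a weighted kappa with 95% CI, in the experimental arm, between the pre-treatment AI grade for the procedure performed and the post-therapy self-evaluation. Report how many patients have no AI grade, separating those who did not request one from those whose matching failed.
- **Wording:** replace the training and train labels with the randomised arm.
- **BCCT.core similarity model:** label it exploratory, unless it is added as an objective.

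The text change is one paragraph. The possible further cost is in data capture: the sponsor has to confirm that the AI grade is stored for each patient who receives one, and add it to Table 2. The choice of time point, kappa weights and bootstrap scheme can stay with the trial team, provided it is fixed in advance.

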**Fig 1 pone.0289365.g001:**
[figure not shown]
Rationale of the randomization method.

The intervention arm will have access to the CINDERELLA platform which entails the information related to surgery and/or radiotherapy. Upon patient’s request, the platform will provide the patient with a matched picture as an example of her own aesthetic outcome according to the surgical procedure she chooses, and an objective evaluation of this aesthetic outcome (e.g., good/fair). The trial will not interfere with the type of locoregional therapy offered to the patient, or any treatment, but will evaluate the CINDERELLA approach and standard approach in terms of achieving an optimized shared decision making.

In total, considering both primary objectives (i) to evaluate the differences between the arms in patient’s agreement of expectations and aesthetic outcome and (ii) in the experimental arm only, the agreement of the AI-evaluation and patient’s post-therapy self-evaluation, it is estimated that a minimum of 515 patients will be enrolled in each arm of the study, based on recent information (frequency and dropout) from the clinical centres. The trial objectives are summarized in Table 1. Sample size was calculated in a two-step simulation-based approach using information from a previous study and expert clinical opinion for the 1^st^ and the 2^nd^ primary objectives, respectively. The simulation studies considered the use of weighted Cohen’s k to calculate the level agreement with a precision of 0.1 and a confidence level of 95% [13, 14]. The proposed sample size was obtained after a 40% correction to account for potential dropout.

**Table 1 pone.0289365.t001:** CINDERELLA trial–objectives.

TRIAL OBJECTIVES

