Eligibility criteria include: Female aged more than 18 years old; written informed consent; primary breast cancer in situ or invasive without evidence of systemic disease (non-Stage IV or locally advanced non-operable breast cancer); ECOG performance status 0 or 1; Uni or Bilateral breast surgery even if prophylactic in one side; Ability to use a web-based app autonomously or with home-based support. Exclusion criteria include: Mastectomy without reconstruction; pregnancy or lactation; Previous radiation to breast/chest (e.g., lymphoma); previous ipsilateral breast surgery due to malignant disease; other neoplasm in the last 5 years (excluding basal cell carcinoma of the skin and adequately treated carcinoma in situ of the cervix); severe skin disease that will contra-indicate the use of radiotherapy; previous breast prophylactic surgery; uncontrolled psychiatric disorder.

After randomization the patient will either follow the investigational arm with the CINDERELLA APProach vs. a conventional approach (control arm). For both study arms, patient’s breasts will be photographed (without identifiers) prior to any intervention. The patients will fill in an expectations questionnaire, resource consumption survey and patient-reported outcome measures (PROMs): EQ-5D-5L, EORTC QLQ C-30 and EORTC BR-23/EORTC QLQ BR-45, Harris Scale, and BREAST Q ICHOM. Questionnaires and photographs will be repeated after healing is completed, six months and one year after the end of treatment (surgery or radiotherapy if radiotherapy was done). Data manager will evaluate that all collected data and questionnaires are completed properly at the time of submission by the centres, to reduce the possibility of missing information and non-compliance with the protocol.

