Investigational arm-only: prior to deciding on locoregional therapy the patient will be given access to the CINDERELLA platform. The platform will contain clinical information as mentioned above. The patient breasts will be photographed prior to therapy by the research team. The BreLO AI (version 1.0) will match the patient biometrics and images with a similar case existent in the BreLO repository and already classified by the BCCT.core (version 4.0) into excellent, good, fair and poor. The patient can then visualize the results presented as synthetized images of her own body. BreLO AI will include an automatic image quality assessment module; if the images of the patient are below a quality standard, the matching will fail with an error message for the user.

All trial information will be fed into the platform to improve the AI-system for performing biomatching. To promote participant retention and complete follow-up, an intense training of nurses in each site as well as continuous proactive follow-up will be ensured. If participants discontinue or deviate from intervention, we will document that event but not obtain any special outcome data.

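### The planned beta regression does not suit a similarity score built from two ordinal grades, which can equal exactly 0 or 1

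*Protocol article*

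**What the plan says.** The Statistical analysis section of the protocol article names three analyses for the primary objectives:

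- Generalised linear models, in particular "multinomial regression models for ordinal data", for the effect of the training on the woman's evaluation of her aesthetic outcome.
- Weighted Cohen's kappa, which "will be calculated for both groups (train and control) and compared using a statistical test and/or bootstrap techniques".
- A per-patient score: "A measure of similarity between self-evaluation and the BCCT.core will be computed for each participant and a beta regression model will be fitted". This model is to estimate the effect of training, adjusted for confounders, "at each time point and in a longitudinal perspective".

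The scales are described elsewhere in Methods. In the paragraph on the investigational arm, the repository cases are "already classified by the BCCT.core (version 4.0) into excellent, good, fair and poor", which gives BCCT.core four ordered grades. The self-evaluation scale is not described. The list of instruments ends with "Harris Scale, and BREAST Q ICHOM" and gives no categories. Table 2 schedules BCCT.core at 6 and 12 months after the end of treatment.

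The article gives no formula or range for the similarity and no treatment of values at 0 or 1.

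**The concern.** Each woman contributes one pair of ratings per visit: her own grade and the BCCT.core grade. A similarity built from one pair of ordinal grades is a short list of discrete values and not a continuous proportion. On a 0 to 1 scale its upper end is reached whenever the two grades coincide. The beta distribution excludes both ends, so the named model fails at exact agreement, which is the result that the intervention is meant to make more frequent.

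The usual repair is to push the boundary values slightly inward. How far to push is arbitrary, and the logit scale of the model magnifies the choice. If the constant is not fixed in advance, the estimated effect of the intervention in this analysis depends on it.

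**Working it through.** The article gives no figure on this point to reproduce. The check has four steps.

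**Inputs.** Four BCCT.core grades (Methods). Four matching self-evaluation grades (assumed; inferred from weighted kappa and the ordinal model). Patients per arm: Methods states that "a minimum of 515 patients will be enrolled in each arm of the study" and that "The proposed sample size was obtained after a 40% correction to account for potential dropout". Read as 40% loss, this leaves 515 × 0.60 = 309 per arm. All agreement patterns below are assumptions, since the article gives no expected kappa or percentage agreement.

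**1. Values of the score.** Let d be the absolute grade difference (0, 1, 2 or 3).
- Linear weights, 1 − d/3: 1, 2/3, 1/3, 0.
- Quadratic weights, 1 − d²/9: 1, 0.889, 0.556, 0.

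Either way there are four values, with 1 at every agreement and 0 at a three-grade gap.

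**2. The beta likelihood at the boundary.** The log-density is (a − 1)·log y + (b − 1)·log(1 − y) − log B(a, b). At y = 1 the second term contains log 0. Evaluated at y = 1, the log-density is −∞ for (a, b) = (5, 2) and (2, 2), and +∞ for (2, 0.5). A standard beta-regression routine rejects data containing 0 or 1.

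**3. Dependence on the repair.** Similarity is taken as 1 − d/3, with 309 per arm, expected counts rounded to whole patients, and boundary values clipped to c and 1 − c for c from 1e-6 to 0.05. Probabilities are for d = 0/1/2/3.

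| Pattern | One arm | Other arm | Arm coefficient or z, c = 1e-6 to c = 0.05 |
|---|---|---|---|
| A: more exact agreement, fewer gaps | .45/.42/.11/.02 | .55/.36/.08/.01 | z 2.14 to 2.32 |
| B: equal exact agreement, fewer large gaps | .50/.30/.15/.05 | .50/.42/.07/.01 | coefficient 0.082 to 0.139; z 0.84 to 1.69; p 0.40 to 0.09 |
| C: more exact agreement, but also more large gaps | .45/.45/.09/.01 | .55/.28/.13/.04 | coefficient 0.111 to 0.038 |

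In B the coefficient grows by a factor of 0.139/0.082 = 1.7. In C it falls by 1 − 0.038/0.111 = 66%. In C the mean similarity is the same in both arms: .45 + .45 × 2/3 + .09 × 1/3 = 0.78, and .55 + .28 × 2/3 + .13 × 1/3 = 0.78. The size of the fitted arm effect there therefore depends heavily on how far the 0s and 1s are moved.

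In pattern A the constant matters little in random samples too. Over 60 simulated data sets, mean z ran from 1.95 to 2.17 across the clips, and whether z passed 1.96 depended on the choice of repair in 3 of 60.

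**4. How often agreement occurs.** With grade margins m, assumed equal for both ratings, and kappa k, the joint table is k·diag(m) + (1 − k)·mmᵀ. Three assumed sets of margins were used: .15/.45/.30/.10, .25 each, and .10/.60/.25/.05.

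- k = 0: agreement 25–44%; a one-grade gap is commoner.
- k = 0.1: 33–49%; either can be commonest.
- k = 0.2: 40–55%; agreement is commonest in all three sets (with equal margins, 0.2 + 0.8 × 0.25 = 0.40).
- k = 0.4: 55–66%.

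Even at k = 0 at least a quarter of the scores sit exactly at 1.

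**The case against.** The strongest reply is that the defect rests on a score that the article does not define. No formula or range is given, and only BCCT.core is stated to have four grades. A condensed article may leave the score and its boundary handling to the full analysis plan, where a squeeze or a zero/one-inflated beta model could be specified. This stands in part. The four-by-four structure is an inference, and the full plan may already contain a remedy. But the article does more than leave a detail out: it names a continuous model for what is, on the natural reading, a four-valued score. An inflated form would run, but its continuous part would still describe only two interior values.

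It is also fair to say that the arbitrary constant changes little in some patterns. Pattern A shows this.

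A reader might go further in four ways that the document does not support:

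- That the model fails for the commonest result. No expected agreement is given. This is plausible from a kappa of about 0.2 but not assured below it.
- That the primary objectives are left without a usable analysis. The ordinal regression and the kappa comparison are unaffected, and the sample size is tied to weighted kappa.
- That the repair will be chosen with the data in view. The full plan is not shown, so this cannot be known.
- That two BCCT.core visits contradict the longitudinal intention. Two visits allow a longitudinal model, so there is no error there.

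**Conclusion.** The point holds in a limited form and should be fixed. Ordinary beta regression, as named, cannot be fitted to a 0 to 1 similarity of two ordinal grades, and the article gives no boundary treatment. The conclusion assumes that the similarity is scaled to include 0 and 1 and that the self-evaluation uses the same ordered grades as BCCT.core. Neither is stated; weighted kappa makes the second the natural reading.

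The consequence depends on the pattern of agreement. Under the assumed patterns with 309 per arm, the choice of clip between 1e-6 and 0.05 ranges from nearly harmless (z 2.14 to 2.32) to multiplying the arm coefficient by 1.7 or cutting it by two thirds. The defect is confined to one of the three analyses named for the primary objectives.

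**What to change.** Replace the beta model with a cumulative-logit mixed model on the grade distance (0 to 3). Include arm, visit (6 and 12 months, when BCCT.core is scheduled), arm-by-visit, the minimisation factors (type of surgery, age group, radiotherapy), centre and a patient random intercept. State the grades of the self-evaluation, so that the distance is defined.

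If a beta model is kept, define the similarity score and specify a zero/one-inflated form before outcome data are seen.

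The cost is wording only: the article already plans ordinal models in R, and standard packages fit this one. The small downside is that the effect is reported as an odds ratio for a closer match and not as a difference in mean similarity.
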